### Outcome measures

#### Primary outcome.

**Balance**. Balance performance will be assessed using the Mini-Balance Evaluation Systems Test (Mini-BESTest). This tool evaluates both static and dynamic balance impairments and identifies the risk of falls. It includes 14 items grouped into 4 domains: anticipatory postural adjustments, reactive postural control, sensory orientation, and dynamic gait. Each item will be evaluated on a 3-point ordinal scale ranging from 0 to 2, where 0 denotes minimal functional performance and 2 denotes optimal function. The total score can reach a maximum of 28 points, representing the absence of risk of falls [37]. The Mini-BESTest has demonstrated excellent test-retest reliability in individuals with PD [38,39].

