### Sample size calculation

Sample size estimation was performed using G*Power software (version 3.1.9.7), taking the primary outcome variable, balance, assessed by the Mini-BESTest scale as the reference. Although the hypothesis anticipates superior outcomes for the experimental IVR intervention compared to the control condition, a two-tailed alternative hypothesis was adopted to maintain a conservative statistical approach. The calculation was based on a repeated measures design involving two groups and three time points, but specifically on the expected difference between groups at the post-intervention time point assuming a moderate effect size (d = 0.71), a significance level of 0.05, and a statistical power of 80%**.** Although the study includes follow-up measurements, this approach provides a conservative estimate expected to offer adequate power for comparisons at follow-up. Because the sample size calculation relies on the expected between‑group difference at the post‑intervention time point, assumptions about the correlation between repeated measurements will not be necessary. Under these conditions, the required sample size was determined to be 50 participants, with 25 allocated to each group. To accommodate an estimated 10% attrition rate, the final target sample was increased to 56 participants (28 per group).

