### Statistical analysis

Statistical analysis will be performed with Statistical Package for the Social Sciences version 29.0 (SPSS Inc, Chicago, IL). The significance level will be 0.05 for all statistical analyses. Descriptive statistics will summarize participants’ baseline characteristics and study outcomes. Categorical variables will be presented as absolute and relative frequencies (n, %), whereas continuous variables will be expressed as mean ± standard deviation or, when appropriate, as median and interquartile range, together with 95% confidence intervals. The Shapiro–Wilk test will assess the normality of continuous variables. To ensure comparability between groups at baseline, appropriate parametric or nonparametric tests will be applied depending on data distribution: t-tests or Mann–Whitney U tests for continuous data, and Chi-square tests for categorical data.

To examine the effects of the intervention across time, linear mixed-effects models will be employed to analyze group‑by‑time interactions across the three measurement points. Significant main or interaction effects will be further explored through Bonferroni-adjusted post hoc comparisons. In cases where data deviate from normality, within-group changes will be analyzed using the Friedman test, followed by Wilcoxon signed-rank tests for pairwise comparisons. Bonferroni correction will be applied to control for multiple testing and Type I error.

Between-group differences at each time point will be examined using independent-samples t-tests (accompanied by Levene’s test for homogeneity of variances) for normally distributed data, or Mann–Whitney U tests for non-parametric data. Categorical outcomes will be compared using Chi-square or Fisher’s exact test, as appropriate.

All analyses will follow the intention-to-treat (ITT) principle, including every randomized participant in the group to which they were initially assigned, regardless of adherence, or protocol deviations. Missing data will be managed through suitable statistical procedures, such as last observation carried forward (LOCF) or multiple imputation, depending on the type and extent of missingness.

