### Strengths and limitations

This study offers strengths, including a novel intervention using an IVR physical therapy program based on levels and dual tasks, which has not yet been implemented in this population. However, the study has some limitations. One limitation is its single-blind design, as participants will be aware of their group allocation, potentially introducing performance bias. To mitigate this, all participants will receive equal attention and session time, and outcome assessors will remain blinded to group assignments to reduce detection bias. Another limitation is the inability to isolate the specific effects of the IVR intervention, since, for ethical reasons, it must be delivered alongside any ongoing individual or group therapies participants are receiving. This will be managed by carefully documenting all concurrent treatments to allow for appropriate adjustments during data analysis. Additionally, there is a potential risk of adverse effects associated with IVR use (such as dizziness or visual discomfort), which could lead to participant withdrawal. To minimize this risk, participants will be closely monitored during sessions, and protocols will be in place for early detection and management of side effects, including gradual adaptation periods and optional breaks during VR exposure.

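### The trial is sized on the post-intervention Mini-BESTest difference, but the analysis leaves two ungated between-group routes at 0.05, and the visit-wise tests ignore baseline

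*Protocol article*

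**What the plan says.** The primary outcome is the Mini-BESTest total. The Sample size calculation section describes a repeated-measures design but rests the number "specifically on the expected difference between groups" at the post-intervention visit, "assuming a moderate effect size (d = 0.71), a significance level of 0.05, and a statistical power of 80" per cent. The test is two-sided: "a two-tailed alternative hypothesis was adopted to maintain a conservative statistical approach". The result is 25 per group, raised to 28 for attrition.

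The Statistical analysis section sets the level: "The significance level will be 0.05 for all statistical analyses". It then describes two between-group analyses:

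- Linear mixed-effects models for group-by-time "interactions across the three measurement points", with Bonferroni-adjusted post hoc comparisons after significant effects.
- In a separate paragraph, "Between-group differences at each time point will be examined using independent-samples t-tests", or Mann-Whitney U tests if the data are not normal.

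Neither is called primary, and the second is not made to depend on the first. A general Bonferroni sentence closes the mixed-model paragraph, directly after the Friedman and Wilcoxon alternatives. The t-test paragraph does not mention Bonferroni.

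Under Strengths and limitations, ongoing therapies are to be handled by "carefully documenting all concurrent treatments to allow for appropriate adjustments during data analysis".

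**The concern.** The contrast that justifies the sample size is not the one that the analysis section singles out, because that section singles out none. A significant interaction, a significant post-intervention t-test or a significant 3-month t-test could each be reported as a positive Mini-BESTest result. Three overlapping chances at 0.05 do not carry a 5% error rate.

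The visit-wise tests also compare raw scores, although every participant is assessed before randomisation. In a trial of about 50 evaluable people, the baseline score is probably the cheapest source of precision available. Tests at each time point would, read literally, also include baseline, where a difference between randomised groups can only be chance.

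**Working it through.** **Inputs.** From the article: d = 0.71, two-sided alpha 0.05, power 80%, 25 evaluable per arm, three visits. The correlation between visits is not given. I assume it is equal across visits and between 0.5 and 0.9.

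**1. The plan's own figure.** The normal approximation is n per arm = 2(z₁₋α/₂ + z₀.₈)²/d².

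- Two-sided: 2(1.960 + 0.842)²/0.71² = 31.1, so 32 per arm and 64 in total. The exact noncentral t gives 33 per arm and 66 in total.
- One-sided: 2(1.645 + 0.842)²/0.71² = 24.5, so 25 per arm and 50 in total. The exact t gives 52.

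The stated 50 is therefore not reproduced with the two-sided inputs. The attrition step is right: 50/0.9 rounds up to 56.

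**2. Power of the raw post-intervention t-test.** The noncentrality is 0.71 × √(25/2) = 2.510 on 48 df. With critical value 2.011, power is 69%.

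**3. Error rate over the routes.** I simulated trials with no effect, 25 per arm and 40,000 trials per correlation. The interaction is a 2-df test on the two changes from baseline with unstructured covariance: F = T²(v − 1)/(2v), v = 48, on 2 and 47 df. The Monte Carlo standard error is about √(0.1 × 0.9/40,000) = 0.0015.

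| Positive if | corr. 0.5 | corr. 0.7 | corr. 0.9 |
|---|---|---|---|
| interaction alone | 0.052 | 0.050 | 0.049 |
| post t-test alone | 0.051 | 0.049 | 0.051 |
| interaction or post t-test | 0.093 | 0.094 | 0.097 |
| interaction or either post-baseline t-test | 0.127 | 0.122 | 0.115 |
| interaction, or either t-test at 0.025 | 0.089 | 0.086 | 0.083 |
| either t-test, read only after a significant interaction | 0.017 | 0.011 | 0.005 |

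As a plausibility check, independent tests would give 1 − 0.95² = 0.0975 for two and 1 − 0.95³ = 0.143 for three. The fifth row reads Bonferroni as covering only the two post-baseline t-tests. The last row is the gated reading.

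**4. Value of the baseline score.** Adjusting for baseline multiplies the residual variance by 1 − ρ², so the effective d is 0.71/√(1 − ρ²), on 47 df.

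- ρ = 0.5: 0.71/√0.75 = 0.820, noncentrality 0.820 × √12.5 = 2.90, power 81%.
- ρ = 0.7: 0.71/√0.51 = 0.994, noncentrality 0.994 × √12.5 = 3.52, power 93%.

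**The case against.** Much can be said for the plan.

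- **Multiplicity.** A reader might infer that the visit-wise tests are uncorrected. The text does not establish that, because the general Bonferroni sentence has no stated limit. If it spans both routes, or if the t-tests are read only after a significant interaction, the error rate is controlled. The article says neither, and the narrower reading still leaves about 8% to 9%.
- **Non-normal data.** The plan then turns to within-group Friedman tests and between-group Mann-Whitney tests. The interaction route may drop out, so the rates above describe the normal-data branch only.
- **Baseline.** It is tempting to say that the plan discards the baseline score. It does not, since the mixed model includes baseline as one of its three measurements. The loss is confined to the visit-wise tests.
- **The 69%.** A reader might blame the t-test for the shortfall from 80%. It comes from the sample size calculation, whose 50 does not fit a two-sided test. Only the gain from 69% upwards belongs to this point.
- **Concurrent therapy.** One might infer that the plan will adjust for therapy that changed after randomisation. The limitations section speaks of ongoing therapies, and candidates are identified during existing physical therapy sessions. Such adjustment is possible but not stated.
- **Level of detail.** The sample size section does point to the post-intervention contrast, and an article may leave model terms to an analysis plan. But this article states both analyses and leaves them in competition, so the problem lies in what is written.

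**Conclusion.** The point holds in this limited form. The sample size rests on one contrast, and the analysis section offers two ungated routes without making that contrast decisive.

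On the normal-data branch, the false-positive rate is about 9% to 10% for the interaction or post-intervention t-test, and about 12% to 13% once the 3-month t-test counts. It is about 8% to 9% if Bonferroni covers only the two t-tests. These figures rest on 25 per arm, normal data and an assumed equal correlation of 0.5 to 0.9, and they move little across that range.

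The power gain from baseline adjustment, from 69% to about 81% or 93%, depends strongly on the baseline-to-post correlation, here assumed to be 0.5 or 0.7. It also takes d = 0.71 in units of the post-intervention SD.

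The change should be made, and it can be made before any outcome is analysed: the Data management section places analysis after data collection ends.

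**What to change.** 1. Name a single primary analysis: the between-group difference in Mini-BESTest at post-intervention, from a mixed model on the post-baseline visits with baseline Mini-BESTest (by visit), group, visit and group-by-visit. Test it two-sided at 0.05 and report the 95% confidence interval.
2. Take the 3-month contrast from the same model and make it secondary.
3. Remove the visit-wise t-tests and their Mann-Whitney alternative as routes to the primary conclusion, so that a normality test cannot change which analysis decides it.
4. State which comparisons the Bonferroni correction covers.
5. A minor point: limit any adjustment for concurrent therapy to status at baseline, because the present text does not exclude changes after randomisation, which the assigned arm could influence. Report therapy during the trial descriptively by arm.

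The cost is statistical wording and one degree of freedom for the baseline covariate at the primary visit. No visit, measurement or participant is added. The mismatch between the stated 50 and the two-sided test needs its own correction in the sample size section. Baseline adjustment may offset it, but that depends on a correlation the article does not give.

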### Intervention

A total of 8 face-to-face physical therapy sessions will be conducted over a 4-week period, with a frequency of 2 sessions per week and a follow-up 3 months after the intervention. Each session will last 40 minutes, divided into 2 separate 20-minute segments.

The first part of the intervention will be the same for both groups and will consist of a usual physical therapy session based on the Modified Fitness Counts (mFC) exercise program [33], during which participants will perform 15 repetitions of eccentric exercises targeting antigravity muscle groups, including the trunk, knee flexors and extensors, and hip extensors. Exercises will be performed either in a sitting or standing position, depending on the specific muscle group involved. Movements will be executed at a slow contraction velocity to minimize compensatory strategies. The duration of the eccentric phase will be a maximum of 3 seconds and 1 second for the isometric hold [34].

The second part of the treatment protocol will differ according to group allocation. In the experimental group, the second part of the intervention will consist of a personalized static and dynamic balance physical therapy program delivered through IVR using the Oculus Quest 2 VR headset and FisioVR^®^ software (Abaco Digital, Zaragoza, Spain). This program includes a series of 360º spherical images depicting urban environments familiar to the participants, designed to simulate realistic scenarios in which various postural activities are performed. The immersive setting allows participants to move and explore the virtual environment with greater freedom, engaging in both static and dynamic balance mechanisms. Throughout the intervention, the physical therapist will continuously monitor on a computer the exact content the patient is viewing in the VR environment.

At the beginning of each session, participants will be seated comfortably while the VR headset is fitted and adjusted to ensure optimal focus and comfort. A brief familiarization phase will follow, during which participants will identify objects and landmarks within the environment to confirm adequate visual clarity. Throughout this initial phase, subjective feedback regarding visual distortion, discomfort, or disorientation will be collected to monitor adaptation to the immersive environment. This phase will last 3 minutes [35].

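### LOCF is listed as a method for missing scores; it copies the end-of-programme score to 3 months, or baseline to both later visits, when the planned mixed model can use the observed scores as they stand

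*Protocol article*

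**What the plan says.** All statements are in the protocol article.

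- **Missing data (Statistical analysis).** Missing data will be handled by procedures "such as last observation carried forward (LOCF) or multiple imputation, depending on the type and extent of missingness".
- **Longitudinal model (same section).** For the group-by-time effect, "linear mixed-effects models will be employed" across three measurement points.
- **Further tests (same section).** "Between-group differences at each time point will be examined using independent-samples t-tests", or Mann-Whitney tests. Friedman and Wilcoxon tests are planned for within-group change when data are not normal.
- **Analysis set (same section).** "All analyses will follow the intention-to-treat (ITT) principle, including every randomized participant in the group to which they were initially assigned".
- **Visits.** Sample size calculation describes "a repeated measures design involving two groups and three time points". Under Intervention, "A total of 8 face-to-face physical therapy sessions will be conducted over a 4-week period", with "a follow-up 3 months after the intervention". The scores are therefore baseline, end of programme (about week 4) and 3 months later. Allocation and blinding places randomization after the baseline evaluation.
- **Loss specific to one arm.** Eligibility criteria and Secondary outcomes provide for withdrawal on the Simulator Sickness Questionnaire (SSQ). Intervention says the SSQ is given to the experimental group at the end of each session.

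**The concern.** With three scores per participant, LOCF does one of two things.

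1. **Only the 3-month score is missing.** The end-of-programme score is copied across, so nothing gained is allowed to fade. Retention is the question the 3-month visit asks, and for these participants the answer is assumed. The Introduction itself describes a disease whose progression treatment does not prevent, so an unchanged score is not a neutral assumption.
2. **The participant leaves before the week-4 assessment.** Baseline is copied to both later visits, so no benefit is recorded. This shrinks the post-intervention difference, the comparison on which the trial was sized. SSQ withdrawals belong here, because the questionnaire follows sessions that all fall within the 4-week programme.

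In both cases the copied value enters the analysis as if it had been measured, with no allowance for uncertainty about the missing score.

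None of this is needed for the main model. A linear mixed model fitted to all observed scores is valid under missing at random without imputation. Because baseline is measured before randomization, every randomized participant has at least one score to contribute.

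**Working it through.** **What the plan supplies.** It gives no figure for the effect of its missing-data method. Its only loss figure is 10% attrition overall, which reproduces: 50 / (1 - 0.10) = 55.6, rounded up to 56, or 28 per group. It gives no loss by arm, no timing of loss and no expected waning, so everything below rests on assumed values and only shows direction and scale.

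**Notation (SD units).** g_E, g_C are the mean gains at week 4 in the IVR and control arms. w_E, w_C are the amounts of gain lost by 3 months. p_E, p_C are the proportions lost. Loss is taken as completely at random within arm.

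**A. Loss before week 4 (baseline copied forward).**

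LOCF estimate at week 4 = (1 - p_E) g_E - (1 - p_C) g_C, so bias = -(p_E g_E - p_C g_C). With equal gains g this is -(p_E - p_C) g.

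- Equal gains of 0.5 SD and 10 points more loss in the IVR arm (0.10 x 28 = about 3 participants): -0.10 x 0.5 = **-0.05 SD** at week 4.
- Same case at 3 months, if 0.4 SD of the gain has faded and 0.1 SD remains: -0.10 x 0.1 = **-0.01 SD**.
- Planned difference of 0.71 SD, with assumed gains of 1.01 and 0.30:
  - 10% lost in each arm: 0.90 x 1.01 - 0.90 x 0.30 = **0.64 SD**.
  - 20% lost in IVR, 5% in control: 0.80 x 1.01 - 0.95 x 0.30 = **0.52 SD**.

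These biases all run against IVR.

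**B. Loss after week 4 (end-of-programme score copied to 3 months).**

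Bias at 3 months = p_E w_E - p_C w_C. With equal waning w this is (p_E - p_C) w.

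- Gains persist (w = 0): bias = **0**, whatever the loss.
- Equal waning and equal loss: bias = **0**.
- Equal waning of 0.4 SD and 10 points more loss in IVR: 0.10 x 0.4 = **+0.04 SD**.
- Extreme case: gains of 1.01 and 0.30 SD both vanish by 3 months, so the true difference is 0.

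| 3-month score missing, IVR / control | LOCF bias (formula) | Two-sided 5% t-test rejects, LOCF | Same test, observed scores only |
|---|---|---|---|
| 10% / 10% | 0.101 - 0.030 = +0.07 SD | 6.2% | 5.1% |
| 20% / 20% | 0.202 - 0.060 = +0.14 SD | 7.9% | 4.8% |
| 20% / 5% | 0.202 - 0.015 = +0.19 SD | 9.8% | 5.3% |

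Rejection rates come from 8,000 simulated trials per row, 28 per arm, with an assumed correlation of 0.7 between visits.

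**Scale.** With 28 per arm and unit SD, the standard error of a difference between arms at one visit is sqrt(2/28) = 0.27 SD. A bias of 0.05 SD is 0.05 / 0.27 = about 0.19 standard errors, and 0.05 / 0.71 = 7% of the planned effect.

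**The case against.** The strongest defence has four parts.

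- **The sentence is illustrative and already names multiple imputation.** True, and multiple imputation is acceptable. LOCF is still named as an admissible method. That is a poor method written into the plan, which differs from detail left to a fuller document.
- **Imputation is not redundant.** This stands. The per-visit t-tests and Mann-Whitney tests and the Friedman and Wilcoxon tests drop incomplete cases unless values are filled in, and the plan says all analyses include everyone randomized. That no imputation is needed is true of the mixed model only, under missing at random.
- **The bias is small and rests on assumptions.** This stands as to size. At moderate inputs it is a fraction of a standard error, and for loss after week 4 it is zero if gains persist. The larger figures above need the whole gain to disappear.
- **The trial is sized on the post-intervention comparison, not on 3 months.** This is correct, but early loss under LOCF affects that comparison too.

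A reader might also infer two stronger charges, and the document supports neither.

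- *SSQ withdrawal makes LOCF favour IVR at 3 months.* SSQ withdrawals arise during the 4-week programme, so LOCF copies baseline for them and the bias runs against IVR. A bias towards IVR under equal waning, such as +0.04 SD, or 0.20 x 0.6 = +0.12 SD with a 20-point difference in loss, needs excess IVR loss after the programme. Nothing in the article points to that.
- *The method could be picked to suit the result.* The stated basis for the choice is the type and extent of missingness, not the outcome or the treatment effect. The absence of a detailed decision rule is something an article may leave to the full plan.

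**Conclusion.** The point holds: LOCF should not be among the permitted methods. It assumes full retention for participants missing only the 3-month score and no benefit for those lost before week 4, and it treats copied scores as data. The mixed model already planned avoids all three problems under missing at random.

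The direction and size of the bias cannot be fixed from the document. Under the assumed values it is about -0.05 SD at week 4 for 10 points of excess early IVR loss with a 0.5 SD gain. For later loss it runs from zero (gains persist) to +0.19 SD in the extreme case tabulated. The only arm-specific cause of loss that the plan describes acts early and so dilutes the effect of IVR. That reading assumes SSQ withdrawals are not assessed afterwards. Secondary outcomes speaks of withdrawal from the study, whereas Intervention speaks of stopping the intervention; if these participants are still assessed, nothing is missing for them.

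This is worth correcting before analysis because the correction is nearly free. It does not by itself put the trial's main comparison in doubt.

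**What to change.** In the Statistical analysis section:

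1. Delete LOCF.
2. Name the linear mixed model on all observed scores, without imputation, as the primary analysis, and state that it relies on missing at random.
3. Where the per-visit and non-parametric tests must include every randomized participant, specify multiple imputation carried out separately by arm, and say how results are combined across imputed data sets.

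Optionally, add a sensitivity analysis that shifts the imputed IVR scores progressively downwards until the conclusion changes. The plan is not wrong for lacking one.

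The cost is a few sentences and a little analysis work. The target of 56 participants is unaffected, and no change to data collection is needed.

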Effect sizes will be computed to determine the magnitude of observed differences, using Cohen’s d for parametric tests and effect size r for non-parametric analyses, both within and between groups for the primary outcomes. Effect sizes will be reported with 95% confidence intervals, and interpretation will consider both statistical significance and clinical relevance, using established Minimal Clinically Important Differences (MCIDs) for all outcomes. Insignificant, small, medium, and large differences will be reflected in effect sizes of < 0.2, 0.2–0.5, 0.5–0.8, and > 0.8, respectively [54].

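### The magnitude bands for effect sizes are Cohen's d bands but are not limited to d, so between-group r from the non-parametric branch would be given too low a label

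*Protocol article*

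**What the plan says.** Protocol article, Statistical analysis: effect sizes are to be computed "using Cohen’s d for parametric tests and effect size r for non-parametric analyses, both within and between groups for the primary outcomes". Shortly afterwards one set of labels is given: "Insignificant, small, medium, and large differences will be reflected in effect sizes of < 0.2, 0.2–0.5, 0.5–0.8, and > 0.8, respectively". The sentence speaks of effect sizes in general and is not limited to d. No other scale appears for r, and the formula for r is not given.

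The same section decides when r is used. If data depart from normality, "within-group changes will be analyzed using the Friedman test, followed by Wilcoxon signed-rank tests for pairwise comparisons". Between-group comparisons at each time point use t-tests, "or Mann–Whitney U tests for non-parametric data".

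The Primary outcome section names the Mini-BESTest total, with a maximum of 28. Of its 14 items it says: "Each item will be evaluated on a 3-point ordinal scale ranging from 0 to 2". The Sample size calculation section plans on a between-group difference, "assuming a moderate effect size (d = 0.71), a significance level of 0.05, and a statistical power of 80" percent.

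**The concern.** Cohen's d is a difference in standard deviation units and has no upper limit. The r that accompanies a rank test is a correlation-type measure and cannot exceed 1. One set of bands cannot describe both, and the limits 0.2, 0.5 and 0.8 belong to d.

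The r branch could well be used for the primary outcome, which is a bounded sum of ordinal items checked with a Shapiro–Wilk test. If it is used, the adjective attached to the main result changes for a reason unrelated to the size of the effect. Labels would also not be comparable between time points that took different branches. The plan makes effect size part of the interpretation, next to statistical significance and minimal clinically important differences, so the adjective is likely to reach the results and discussion text.

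**Working it through.** **Inputs.** The bands 0.2/0.5/0.8 and the two metrics come from Statistical analysis. The values d = 0.71 and 25 per group come from Sample size calculation, and 1:1 allocation from Allocation and blinding. The bands are conventions, so there is no figure of the plan to reproduce. Assumption, because no formula is stated: r = Z/√N.

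**Between groups, d to r.** For two equal groups r = d/√(d² + 4).
- d = 0.2: 0.2/√4.04 = 0.10
- d = 0.5: 0.5/√4.25 = 0.24
- d = 0.71: 0.71/√4.5041 = 0.33
- d = 0.8: 0.8/√4.64 = 0.37

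Cross-check for the Mann–Whitney r with normal data in large samples, r = √3·(Φ(d/√2) − 0.5): this gives 0.097, 0.239, 0.333 and 0.371 for the same four values.

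**Between groups, r to d.** d = 2r/√(1 − r²).
- r = 0.2: 0.4/√0.96 = 0.41
- r = 0.5: 1/√0.75 = 1.15
- r = 0.8: 1.6/0.6 = 2.67

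**Labels side by side (between groups).**

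| d | Label on d | Equivalent r | Label if the bands are read as r |
|---|---|---|---|
| below 0.20 | insignificant | below 0.10 | insignificant |
| 0.20–0.41 | small | 0.10–0.20 | insignificant |
| 0.41–0.50 | small | 0.20–0.24 | small |
| 0.50–0.80 | medium | 0.24–0.37 | small |
| 0.80–1.15 | large | 0.37–0.50 | small |
| 1.15–2.67 | large | 0.50–0.80 | medium |
| above 2.67 | large | above 0.80 | large |

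The planning effect, which the plan itself calls moderate, falls in the fourth row.

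**Ceiling.** With complete separation of two groups of 25, Z = 312.5/√(625 × 51/12) = 6.06, and r = 6.06/√50 = 0.857. The *large* band for between-group r therefore runs only from 0.80 to 0.857.

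**Simulation.** With normal data, 25 per group, true d = 0.8 and 5,000 runs, the mean Mann–Whitney r was 0.37. The label was *small* in 76% of runs, *medium* in 15%, *insignificant* in 9% and *large* in none. The 9% reflects sampling variation around 0.37, not the conversion.

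**Within groups.** The two-group conversion does not apply to the Wilcoxon signed-rank test. For normal changes in large samples, with d the mean change divided by the SD of the change, Z/√pairs tends to √3·(Φ(√2·d) − 0.5). Dividing by √observations instead lowers this by a factor √2.

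| Standardised change | r, divisor √pairs | r, divisor √observations |
|---|---|---|
| 0.2 | 0.19 | 0.14 |
| 0.5 | 0.45 | 0.32 |
| 0.8 | 0.64 | 0.45 |

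A change of 0.8 would be *medium* with the first divisor and *small* with the second. With the second, r cannot exceed about 0.62 at 25 pairs, so *large* could not occur.

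**The case against.** The strongest objection is that the plan nowhere says outright that the bands govern r. They are the familiar d bands, and the authors may have meant only d. An analysis plan not shown here may define r and its benchmarks. This stands as a limit on certainty: what will be done with r is inferred from an unrestricted sentence and the absence of any other scale. It does not remove the point, because the rule as printed covers both metrics and is wrong for one of them. If only d was meant, the sentence still needs that restriction.

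The consequences are also limited, and that stands. Effect sizes are planned only for the primary outcome, and r arises only if that outcome takes the non-parametric branch. The plan also commits to 95% confidence intervals for effect sizes and to minimal clinically important differences, so the adjective is not the only guide.

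A reader might infer more than the figures support:
- *Every large effect would be reported as small.* This holds only for a between-group d of about 0.8 to 1.15. From about 1.15 to 2.67 the label becomes medium.
- *A medium or large effect could be converted to insignificant.* It could not. An r below 0.2 means d below about 0.41, which is at most small on the d scale.
- *The same shift applies within groups.* There it depends on the divisor for r, which the article does not state.

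**Conclusion.** The point holds as a defect in a stated rule. Followed as written, the bands give between-group r a lower label than d for the same effect over most of the range: the planning effect drops from medium to small, d of about 0.8 to 1.15 from large to small, and d of about 1.15 to 2.67 from large to medium. The label on the primary result would depend on the outcome of the normality check.

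This rests on reading the unrestricted sentence as covering r, on r = Z/√N, on two groups of equal size and on approximately normal data for the conversion. Only the verbal interpretation is affected. No p-value, test decision or sample size changes.

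**What to change.** State that the bands 0.2/0.5/0.8 apply to Cohen's d only. Then choose one of two routes:

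1. Report one effect-size scale for the primary outcome whichever test is used, so that labels stay comparable.
2. Keep r, state its formula including the divisor for paired data, and give it separate bands. For between-group comparisons with equal groups, the equivalents of the d bands are about 0.10/0.24/0.37. Within-group comparisons need their own bands, matched to the chosen divisor: on the large-sample normal approximation, about 0.19/0.45/0.64 with √pairs or 0.14/0.32/0.45 with √observations.

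The between-group values must not be used for paired Wilcoxon r. With the √pairs divisor, r = 0.37 is a standardised change of only about 0.40 (√3·(Φ(√2 × 0.40) − 0.5) ≈ 0.37), so a small change would be labelled large.

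The cost is one or two sentences. The Data management section places the analysis after recruitment and data collection are complete, so the text can be settled before any effect size is computed.
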